## 2.2 Specific objective

i. To determine the effect of albendazole administration with a fatty meal such as avocado, versus albendazole administration without a fatty meal, on hookworm cure rate and egg reduction rate.

ii. To determine the effectiveness of dual-dose (400mg/day, two consecutive days) versus single-dose (400mg) albendazole treatment regimens on hookworm cure rate and egg reduction rate.

iii. To identify and evaluate environmental, social and cultural variables affecting hookworm infection, and cure rate and egg reduction rate of albendazole against hookworm.

1. Methodology

This study will be embedded within the framework of the MANE project. The baseline prevalence survey was completed in July 2019, and the second prevalence survey is scheduled in September 2021 to evaluate the impact of programs implemented between 2019 and 2021.

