## 3.2 Study design, inclusion and exclusion criteria

The study will have two phases. The first phase will be a descriptive cross-sectional study which will evaluate the prevalence of STHs and schistosomiasis in Mayuge district as the follow-up survey of the MANE project.

In the second phase, children who have hookworm infection in this cross-sectional survey, will then take part in a randomised controlled trial with factorial design to assess impact of dual- vs single-dose albendazole and impact of taking albendazole with fatty foods on cure rate and egg reduction rate. Outcomes will be assessed at a follow-up visit 21 days after albendazole treatment.

In Mayuge district, primary four and primary five students will be the target population. Target schools will be selected and a given number of the sample from each selected school confirmed. Children whose parents/guardian signed consents for the children participating in the prevalence survey, and in the nested trial if hookworm infection is detected, will be included.

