**For phase II:**

For the trial phase of the study, the aim is to assess the effect of co-administration with fatty foods, and of dual-dose versus single-dose albendazole on hookworm cure rate. The cure rate of single dose albendazole for hookworms varies between 36% and 93% in previously reported studies. Based on data from Adegnika et al (42), we power our trial to detect a difference in cure rate of 70% versus 50% for both co-administration with fatty foods versus no co-administration, and for dual-dose versus single-dose albendazole.

With type I error probability of 5%, 93 participants in each comparison group will be required for 80% power to detect a difference in cure rate of 70% versus 50%. Therefore, the total target sample size for the trial will be 186. However, allowing for 5% loss to follow-up, i.e. 5% of hookworm positive cases not appearing on the follow up stool test 21 days after treatment, the target sample size will increase to 196. If the expecting prevalence of hookworm in 2021 is 12%, to satisfy the sample size of 196, the target sample size of the prevalence survey of 2021 will be 1,634. Therefore, a total sample size of 1,650 will be sufficient to cover sample size requirements of both the prevalence survey and the nested trial.

Assuming that 50 children will be selected from each school, a total of 33 schools will be randomly selected in order to achieve the required sample size.

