When analysing the results of the trial of fatty meal co-administration with single-, and dual-dose albendazole, the primary outcomes will be cure rate and egg reduction rate among four different groups, Chi-square (χ2) test will be applied for analysing the difference of cure rate among four treatment groups. Differences in eggs count between enrolment and follow-up will be assessed by using paired t-test. Chi-square (χ2) test or Fisher’s exact test will be applied to assess categorical variables on the difference of cure rate with four different options of treatment against hookworm. χ2 Test for trend will be used to evaluate ordered categorical variables on the difference of cure rate with four different treatment options against hookworm.

- - **Precautionary measures for the prevalence survey in the context of COVID-19**.

The WHO published the interim guideline of conducting a variety of NTDs related activities in the context of COVID-19 in the name of considerations for implementing mass treatment, active case finding and population-based surveys for neglected tropical diseases in the context of COVID-19 pandemic: interim guidance(43). According to this guideline, for conducting prevalence survey safely during the COVID-19 pandemic situation, there must be following precautionary measures as indicated in the WHO guideline. There are considerations how to take precautionary measures applicable to designated sites for planned activities (table 3 in the interim guidance), precautionary measures for health staff and community health workers (table 4 in the interim guidance), and precautionary measures for the target population(table 5 in the interim guidance).

1. Dissemination Plan

This survey will be conducted with multiple stakeholders including the ministry of health of Uganda, donor organisation (KOICA), scientists from academic partners (London School of Hygiene and Tropical Medicine), policymakers, and health professionals. The results will be written and made academic transcripts for dragging attention to reducing the NTDs burden in Uganda. The results will not reflect any personal information.

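### The cure-rate test compares four arms, but the trial is sized on two pooled comparisons, so the stated test is not the one powered and cannot answer objectives i and ii

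*Protocol*

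**What the plan says.** Section 2.2 sets two treatment objectives, each a contrast between two levels. Objective i is "To determine the effect of albendazole administration with a fatty meal such as avocado, versus albendazole administration without a fatty meal". Objective ii is "To determine the effectiveness of dual-dose (400mg/day, two consecutive days) versus single-dose (400mg) albendazole treatment regimens on hookworm cure rate". Section 3.2 calls the second phase a "randomised controlled trial with factorial design to assess impact of dual- vs single-dose albendazole and impact of taking albendazole with fatty foods".

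The phase II paragraph of section 3.6.1 follows that structure. The trial is powered for "70% versus 50% for both co-administration with fatty foods versus no co-administration, and for dual-dose versus single-dose albendazole", and "93 participants in each comparison group will be required for 80% power". The total is 186 evaluable children, raised to 196 for 5% loss. Section 3.4 allocates equally to four arms within blocks of eight, stratified by health facility.

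For the trial's cure rate, section 3.7.1 says that a chi-square "test will be applied for analysing the difference of cure rate among four treatment groups". The two later sentences on cure rate (chi-square or Fisher's exact test, and a trend test) also refer to four treatment options. The logistic regression in the same section concerns risk factors for prevalence in the survey, not the trial.

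**The concern.** A total of 186 gives 93 per side for both factors only if each arm is counted twice, once by dose and once by avocado. That is the usual economy of a factorial design, and it requires an analysis that pools arms across the other factor. Section 3.7.1 instead names a comparison across the four arms, with about 46.5 evaluable children each.

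Two things are at stake. First, the stated 80% belongs to a test that the analysis section does not name. Second, a four-group p-value cannot be assigned to dose or to avocado and yields no effect estimate for either, yet section 2 says that the results are meant to guide the choice of mass-treatment option. Cure rate is a primary outcome, so the gap affects both treatment objectives. It also leaves the choice of contrast open until after the data are seen.

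**Working it through.** **Inputs.** From section 3.6.1: cure rates 50% and 70%, type I error 5%, power 80%, 93 per comparison group, 186 in total, 196 with 5% loss. From section 3.4: equal allocation to four arms. From Fig 1: 53 per arm, 212 in total, used as a sensitivity case. Assumption: two-sided test. The protocol does not state sidedness, but two-sided gives 93 and one-sided gives 74.

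**Step 1: the plan's own figure.** With pooled variance, mean rate 0.60 and no continuity correction,

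n = [1.960·√(2·0.6·0.4) + 0.842·√(0.5·0.5 + 0.7·0.3)]² / 0.20² = (1.358 + 0.571)² / 0.04 = 93.0.

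So 93 per side is reproduced. Power at 93 v 93 is Φ[(0.20·√93 − 1.960·√0.48)/√0.46] = Φ(0.842) = 80.0%. And 186/0.95 = 195.8, so 196.

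**Step 2: the stated test, read as a 3-df chi-square.** The noncentrality is λ = n_arm·Σ(pᵢ − p̄)² / [p̄(1 − p̄)], and power is the chance that a noncentral chi-square with 3 df exceeds 7.815. With 186 analysed, n_arm = 46.5.

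*Only one factor works* (arms 50/50/70/70%). Here p̄ = 0.60 and Σ = 4·0.01 = 0.04, so λ = 46.5·0.04/0.24 = 7.75 and power is 63.9%. Simulation with 200,000 replicates gives 64.3% for the four-group test and 79.8% for the pooled test of the active factor.

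| Number analysed | Four-group test | Pooled test of the active factor |
|---|---|---|
| 186 | 64% | 80% |
| 196 | 66% | 82% |
| 212 | 70% | 85% |

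The last two rows assume that nobody is lost. After 5% loss, 212 leaves about 201 (about 50 per arm), and the figures are 68% and 83%. For 80% power in this case the four-group test needs about 66 per arm, or 264 evaluable children.

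*Both factors work additively* (arms 40/60/60/80%, so each pooled contrast is 50% v 70%). Σ = 0.08, λ = 46.5·0.08/0.24 = 15.5, and power is 92.6%. That is power against the hypothesis that all four arms are equal. Each pooled test has 80% for its own factor.

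*Sub-additive effects* (arms 50/70/70/70%). p̄ = 0.65, Σ = 0.0225 + 3·0.0025 = 0.03, λ = 46.5·0.03/0.2275 = 6.13, and power is 52.8%. The pooled contrasts shrink to 60% v 70%. In simulation each has about 30% power, and at least one of the two rejects in about 50% of trials.

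**Step 3: error rate of the two pooled tests.** Two independent tests at 5% give a family-wise error of 1 − 0.95² = 9.75%.

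**The case against.** The strongest reply is that the four-group test is not always weaker. A reader might infer that it falls short of 80% whatever the truth. The documents do not support that. Section 3.6.1 posits the effect for both factors, and if both work additively the test rejects in about 93% of trials. With sub-additive effects, 53% is above the 30% of either pooled test. This part of the reply stands: the power loss is specific to the case where one factor works and the other does not. It does not rescue the objectives, because rejecting equality of four arms does not identify the factor responsible.

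A second reply is that section 3.7.1 gives neither the number of tests nor the degrees of freedom, so the wording may be loose and a separate analysis plan may name the pooled contrasts. That is possible, and the 3-df reading is an interpretation. But the section refers repeatedly to four groups or options and never to a pooled contrast. An analysis plan that used pooled contrasts would depart from the protocol's stated test.

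A reader might also infer that a significant result would be followed by underpowered arm-by-arm tests. The protocol plans no such tests, and pooled contrasts can still be computed from the four-arm data, so no power for arm-by-arm tests is counted here.

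**Conclusion.** The mismatch is real and lies in what the protocol states. The sample size is right for two pooled comparisons, but the named cure-rate test is across four arms. It answers neither objective i nor objective ii, whichever scenario holds. Its cost in power is conditional: about 64% instead of 80% at 186 evaluable children if only one factor has the 70% v 50% effect, with a gap of about 15 percentage points at the other sample sizes in the protocol. A flat statement that the test lacks 80% power would go too far.

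These figures assume a two-sided 5% level, equal arms, no continuity correction and a single 3-df test.

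**What to change.** In section 3.7.1, make the two pooled comparisons, dual v single dose and avocado v none, the primary cure-rate analyses. Use one model containing both factors and the health-facility stratum: either a binomial model for the risk difference, or a logistic model with standardised risk differences, since logistic coefficients alone do not give a difference in cure rate. Report each difference with its 95% CI. State either that each factor is tested at 5%, accepting a family-wise error of up to about 10%, or how this is adjusted. Show the dose-by-avocado interaction and the four arm cure rates alongside, and keep the four-group chi-square as descriptive.

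The cost is one paragraph of wording, with no extra children, visits or data. The downside is that each main effect averages over the other factor, so 80% per factor holds only without material interaction on the risk-difference scale. The interaction estimate should therefore always be read with the main effects.

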**3.7.1 Data analysis**

The MANE team will use Open data kit (ODK) of World Vision for data generation, collection and store

1. ODK build: pre-tested questionnaire questions will be transferred into ODK format.
2. ODK collect: pre-trained field workers will collect data from the participants during the prevalence survey
3. ODK aggregate: collected data will be uploaded and stored into World Vision ODK server.

Data saved in the ODK system will be exported into Microsoft Office Excel, and the data will be checked errors, any missing values, and extreme values. The cleaned data will be exported to the statistic program (Stata or R).

Prevalence of STHs and schistosomiasis with 95% confidence intervals will be calculated. The arithmetic eggs count will be obtained from the microscopic examination of the Kato-Katz method applying made slide. A multiplication factor of 24 should be applied to calculate eggs per gram, since the stool quantity in a slide prepared with the Kato-Katz method contains 41.7mg of the stool. The intensity of infection will be categorised by the criteria of WHO guideline as below(13).

|  | Light intensity infections | Moderate intensity infections | Heavy intensity infections |
| --- | --- | --- | --- |
| *A. lumbricoides* | 1-4,999 epg | 5,000-49,999 epg | ≥ 50,000 epg |
| *T.trichiura* | 1-999 epg | 1,000-9,999 epg | ≥ 10,000 epg |
| Hookworm | 1-1,999 epg | 2,000-3,999 epg | ≥ 4,000 epg |
| *S.mansoni* | 1-99 epg | 100-399 epg | ≥ 400 epg |

(Table 2) The threshold of infection intensity by each STH and *S.mansoni*

I will analyse the relationship between the prevalence and the risk factors from the questionnaire survey. Chi-square (χ2) test or Fisher’s exact test will be applied to assess categorical variables on the prevalence of STHs and schistosomiasis. χ2 Test for trend will be used for evaluating ordered categorical variables on the prevalence of STHs and schistosomiasis. The univariate analysis will be carried out to identify the association between potential risk factors and prevalence. I will conduct multivariate logistic regression analysis to determine which risk factors are associated with the outcomes of the prevalence of STHs and schistosomiasis, with the risk factors significantly (p-value < 0.05) associated with hookworm and schistosomiasis infection.

Continuous variables such as eggs counts for the dependent variable will be assessed by using t-test.

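### The only trial test named for egg counts is a before/after paired t-test, which does not compare egg reduction between doses or between avocado and no avocado

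*Protocol*

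**What the plan says.** Section 2.2 sets two between-group questions, each covering both outcomes. Objective i compares albendazole with a fatty meal "versus albendazole administration without a fatty meal, on hookworm cure rate and egg reduction rate". Objective ii compares dual dose "versus single-dose (400mg) albendazole treatment regimens on hookworm cure rate and egg reduction rate". Section 3.2 describes a "randomised controlled trial with factorial design to assess impact of dual- vs single-dose albendazole" and the impact of fatty food.

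The trial paragraph of section 3.7.1 states that "the primary outcomes will be cure rate and egg reduction rate among four different groups". For cure rate it names a between-arm analysis: a chi-square "test will be applied for analysing the difference of cure rate among four treatment groups". For egg counts it says: "Differences in eggs count between enrolment and follow-up will be assessed by using paired t-test". The remaining tests in that paragraph (chi-square or Fisher's exact, and chi-square for trend) are all tied to cure rate.

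One other sentence in section 3.7.1 mentions egg counts: "Continuous variables such as eggs counts for the dependent variable will be assessed by using t-test". It closes the survey risk-factor text, before the trial analysis begins.

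**The concern.** A paired t-test of enrolment against follow-up asks whether counts fell. The objectives ask whether they fell more with one regimen than with another. Section 3.4 gives albendazole to every arm, including control, and section 3.2 enrols only children found positive. A fall is therefore expected everywhere, part of it from regression to the mean after selection on a positive count.

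If the text is followed, one of two primary outcomes yields no randomised comparison. A significant before/after fall could be presented as evidence for a regimen. If the test is run arm by arm, it invites the reading that a regimen works because its p-value is below 0.05 and another's is not. That is not a test of a difference between arms.

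There is also a mismatch of scale. Egg reduction rate is a relative measure, while the paired t-test works on absolute differences in counts.

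**Working it through.** **1. The protocol's own figure.** Section 3.6.1 gives 93 per comparison group for cure rates of 70% v 50%, 5% type I error and 80% power. Taking a two-sided test with pooled variance and no continuity correction, with a mean proportion of 0.6:

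n = [1.96 × √(2 × 0.6 × 0.4) + 0.842 × √(0.7 × 0.3 + 0.5 × 0.5)]² / 0.2² = (1.358 + 0.571)² / 0.04 ≈ 93.

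Then 2 × 93 = 186, and 186 / 0.95 = 195.8, rounded up to 196. The figures reproduce. They concern cure rate only; the protocol states no sample size or power for egg reduction rate.

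**2. Which hypothesis is tested.** Let B and F be a child's counts at enrolment and follow-up, and take the egg reduction rate (ERR) in an arm as 1 − mean(F) / mean(B). The mean change in that arm is then mean(B) × ERR.

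- Paired t-test null: mean(B − F) = 0.
- Null for the objectives: ERR(dual) = ERR(single), and ERR(avocado) = ERR(no avocado).

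Assume a mean baseline of 400 epg, a figure the protocol does not give:

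- 80% reduction in all four arms: mean change 400 × 0.80 = 320 epg.
- 80% with single dose and 95% with dual dose: (400 × 0.80 + 400 × 0.95) / 2 = 350 epg.

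The paired null is false in both cases, but the arms differ only in the second. This step does not depend on the assumed baseline.

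**3. Illustration.** Assumptions: 46 per arm (186 / 4 = 46.5), mean baseline 400 epg, gamma shape 0.3 to 1.0, overdispersed follow-up counts, 1,500 simulated trials per scenario. Ranges run over the shape values. The protocol does not say whether the paired test is done on all children or by arm, so both are shown.

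| True reduction | Paired test significant, all children | Paired test significant in all four arms |
|---|---|---|
| 60% in every arm | 96.7–99.7% | 35.6–63.3% |
| 80% in every arm | 99.9–100% | 92.3–99.5% |
| 95% in every arm | 100% | 99.9–100% |
| 80% single v 95% dual | 100% | 95.9–99.4% |
| 60% single v 95% dual | 99.5–100% | 60.2–79.0% |

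On all children together, the result is almost the same with and without an arm difference. By arm, significance in all four is the usual result at 80% or more. With 60% everywhere, at least one arm misses significance in 36.7–64.4% of trials (100 − 63.3 and 100 − 35.6), although the arms are identical. An arm-by-arm reading would then report a difference that does not exist.

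A second illustration with a less variable response (47 per arm, mean 200–600 epg, dispersion 0.3–1, 800 trials per scenario) gave significance in all four arms in 100% of trials, both with 80% everywhere and with 70% v 85%.

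**4. Scale.** Section 3.7.1 puts heavy hookworm infection at 4,000 epg or more, and one egg on a slide equals 24 epg. An 80% reduction is a fall of 3,200 epg from 4,000, but of 192 epg from 240. The relative effect is the same, yet the absolute falls differ by a factor of 3,200 / 192 ≈ 17. A few heavy infections can dominate a t-test on raw differences.

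**The case against.** **The paired test is attached to egg counts, not to egg reduction rate.** It could be a before/after description, with the between-arm method left to an analysis plan that is not shown. This has some force, since the link to egg reduction rate is inferred. But it is the only trial test that uses egg counts, and it stands directly after the outcomes and their four-group chi-square. A reader following the protocol would take it as the efficacy test. That makes it a stated test that does not answer the stated question, rather than detail left for later.

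**The general t-test sentence could cover arm comparisons.** It is in the same section and is not expressly limited to the survey. By position, however, it belongs to the risk-factor text. It names no arms, no change and no reduction rate, and a two-sample t-test cannot compare four groups at once.

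**A reader might infer that the trial never compares its randomised arms.** The documents do not support that. Cure rate has a between-arm chi-square test and carries the whole sample size, so randomised evidence on both questions remains.

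**A reader might also infer that one model, such as ANCOVA on log(epg + 1), is required because of its power.** That does not follow. The smallest non-zero count is 24 epg, so such an analysis is driven partly by zero v non-zero and overlaps with cure rate. Any power figure would also rest on an egg-count distribution that the protocol does not give.

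**Regression to the mean affects all randomised arms alike.** True: it distorts the before/after figure but would not bias a between-arm contrast.

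**Conclusion.** The point stands for egg reduction rate and for that outcome only. The test named in section 3.7.1 has a null hypothesis that is expected to be false whenever albendazole works, so its result says nothing about objectives i and ii. This follows from the design (active drug in every arm, entry on a positive count) and needs no simulation.

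The percentages above rest on assumed baseline counts, dispersion and response. They illustrate the point and do not estimate what this trial will see. Significance in every arm is likely when efficacy is high, but it is not certain. No power figure for egg reduction rate should be quoted. The cure-rate analysis and the 93 / 186 / 196 calculation are not affected.

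**What to change.** In the trial paragraph of section 3.7.1:

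- Keep the enrolment-to-follow-up change as description, by arm, without using it as the efficacy test.
- State that egg reduction will be compared between the randomised factor levels, dual v single dose and avocado v none, adjusting for baseline count, with a method suited to skewed, zero-heavy counts. Two suitable options are negative binomial regression of day-21 counts on dose, avocado and baseline count, or the difference in arithmetic-mean egg reduction rate with a bootstrap 95% confidence interval. Others would serve.
- Use one scale for both the test and the reported egg reduction rate, so that the two cannot disagree.
- Say whether the general t-test sentence applies to the survey only.

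The cost is wording. Both egg counts are already collected, and the sample size does not change. The choice should be fixed before follow-up counts are examined by arm.
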